### Sample size {14}

We plan to enroll a total of 374 youth-parent dyads across all participating study sites. Three hundred sixty-eight participants will be included in the analyses. The six other participants are considered “training participants,” who will not be randomized and will receive treatment pathway 1 (all intervention components) for the purpose of providing an opportunity for each interventionist to practice intervention delivery with 1–2 families prior to the enrollment of actual study participants. Power analyses were conducted using FactorialPowerPlan SAS Macro for Aims 1 and 3, and PASS for Aim 2 to determine the appropriate number of participants for the study. The factorial design involves 3 completely crossed factors, and thus the same power calculation applies to each factor being tested, and to interaction effects also, since this is a 2^3^ factorial. Based in part on prior investigations by the study team,^1^ assumptions include: 5 assessment points (baseline, 6 weeks, 3 months, 6 months, and 12 months), within-subject correlations over time of *ρ* = 0.6, two-tailed alpha = 0.05, and 10% 12-month attrition were used for all power analyses. In the prior single-site R01 trial, the study team observed 6–12-month HBI treatment effects ranging between 0.26 and 0.32 and PedsQL treatment effects ranging between 0.19 and 0.29. The proposed sample size of 368 (184 per factor present vs. absent comparison) provides power > 0.80 to detect a small effect size of Cohen’s *d* = 0.15 under these assumptions. In terms of the cell size of the factorial design, we will allocate 46 participants to each of the 8 groups and retain an average of 42 participants within each. In terms of power to detect mediation for Aim 2, with “a” the standardized coefficient between the component group and the mediators = 0.34, “b” the standardized coefficient between the mediators and PedsQL/HBI symptom outcomes = 0.34, and with 368 patients, 10% attrition and alpha set at 5%, the power = 0.80 to detect minimal indirect/mediated effect 0.12 [54]. With a total sample size of 368, the component group by moderator interaction effect size was estimated using ANCOVA with baseline HBI or PedsQL as the covariate. With the probability of a 2-tailed type I error set at 5%, the study will have ≥ 0.80 power to detect a component group by moderator interaction ES = 0.25 for 12-month HBI or PedsQL.

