## Statistical methods

### Statistical methods for primary and secondary outcomes {20a}

#### Aim*** 1***

For Aim 1, the primary purpose of the statistical analyses is to determine whether the three intervention components (a) cf-CBT, (b) PST, and (c) CM each contribute significantly to improvements in post-concussive symptoms (HBI) and youth HRQoL (PedsQL). We hypothesize that over the course of the 12-month trial, families who receive cf-CBT, PS, or CM will demonstrate greater improvements in the primary outcomes compared to those who do not receive these components but that they may be differentially beneficial, suggesting that a streamlined intervention may be comparably effective. To examine this hypothesis, we will perform two sets of analyses. The first set of analyses will examine the effects of individual components (cf-CBT, PST, CM). Towards this end, we will use effect coding of variables for the three components and fit mixed regression models with the following conditional mean structure specification:$$E\left(Y_{ij}\right|b_{0i})=\beta_0+\beta_1cfCBT_i+\beta_2PST_i+\beta_3CM_i+\beta_4Time_j+\beta_5cfCBT\times Time_j+\beta_6PST_i\times Time_j+\beta_7CM_i\times Time_j+\beta_8cfCBT_i\times PST_i+\beta_9cfCBT_iCM_i+\beta_{10}PST_i\times CM_i+other\;interactions+\gamma X_i+b_{0i}$$

where $$cfCBT_i\;=\;1$$  if patient $$i$$ received cfCBT, 0 otherwise, same for PST and CM. The*ot*ℎ*er interactions* include all other two-, three-, and four-way (3 components and time) interaction terms. Based on the mixed models, we can perform repeated ANOVA and test the main effects of each of the three components on our primary outcomes. We will also test for interactions between components.

The second set of analyses will examine the differences across the combinations of the three intervention components as a whole, and identify better-performing combination(s). For this analysis, regardless of linear or generalized linear models, the mean structure for mixed effects regression models can always be specified as

$$(Y_{ij})\;=\;\beta_0\;+\;\beta_1CHIP_i\;+\;\beta_2Time_j\;+\;\beta_3CHIP_i\;\times\;Time_j\;+\gamma X_i\;+b_{0i}$$

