where *Y*_*ij*_ is the outcome for subject *i* at time *j*, *b*_0*i*_ is the subject-specific random intercept to account for within-subject correlation due to repeated measures, and *CHIP*_*i*_ × *Time*_*j*_ is the intervention-by-time interaction term. *CHIP*_*i*_ takes value 1–8 representing each of the 8 combinations of cf-CBT, PS, and CM. *X*_*i*_ is a vector of covariates including baseline injury severity, birth sex, and referring site. We will model *Time*_*j*_ as a discrete variable given a limited number of assessments, the coefficients of the intervention-by-time interaction β_3_ estimate the mean differences between treatment arms in changes (“difference-in-differences”) at later time points relative to baseline. The significance of these coefficients will be assessed using confidence intervals, and *p*-values from *F*-tests based on ANOVA and the Kenward-Roger method [55]. For Aim 1a, we will examine component effects on youth headache, depressive symptoms (PHQ-9) and sleep (ASWS), and parental distress regarding their child’s illness (PIP) using the same methods.

Using our importance criteria, for intervention optimization, we will consider any components or interactions demonstrating an effect size of 0.20 on either the HBI or PedsQL to be worth retaining in the optimized intervention. We will make our initial decision at 6 months, but will also examine 12-month HBI and PedsQL outcomes. We are balancing effectiveness and efficiency in our optimized intervention by not including components that demonstrate a small effect (Cohen’s *d* = 0.20) at 6 or 12 months on the HBI or PedsQL.

#### Aim 2

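### A random intercept as the only device for repeated measures makes the 12-month intervals and tests too optimistic if correlation falls as the gap between visits grows

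*Protocol article*

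**What the plan says.** Under Statistical methods {20a}, Aim 1, both model equations contain one subject-level term. The text describes it as a "subject-specific random intercept to account for within-subject correlation due to repeated measures". No random slope, residual correlation, visit-specific variance or robust variance is mentioned.

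Time enters "as a discrete variable given a limited number of assessments", and the intervention-by-time coefficients "estimate the mean differences between treatment arms in changes" from baseline at each later visit. Inference is by confidence intervals and by F-tests "based on ANOVA and the Kenward-Roger method". For the individual components, the article adds that "we can perform repeated ANOVA and test the main effects of each of the three components on our primary outcomes".

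Sample size {14} lists five assessments, at 0, 1.5, 3, 6 and 12 months. It assumes "within-subject correlations over time of" 0.6, a single value for all pairs of visits, with "two-tailed alpha = 0.05, and 10% 12-month attrition". The retention rule in Aim 1 is an effect size of 0.20 on either primary outcome, judged first at 6 months and then also at 12 months.

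**The concern.** A random intercept with independent, equal-variance residuals is compound symmetry: one variance, and one correlation for every pair of visits. Every change-from-baseline contrast then receives the same modelled variance, whether the gap is 6 weeks or a year.

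That is hard to defend here. Adjacent visits are 1.5 to 6 months apart, participants enter 1 to 12 months after injury, and treatment falls in the first 12 weeks. The article's own background refers to differing symptom trajectories among youth in the earlier trial. If correlation falls with the gap, the model overstates uncertainty at early visits and understates it at 12 months. Kenward-Roger allows for having estimated the parameters of the assumed structure; it does not detect or correct a wrong one.

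At stake are the confidence intervals and p-values for the 12-month contrasts on both primary outcomes, and on the Aim 1a outcomes, which use the same methods.

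**Working it through.** **Inputs.** From Sample size {14}: common correlation 0.6, visits at 0, 1.5, 3, 6 and 12 months, two-sided alpha 0.05, N = 368 with 10% attrition (368 × 0.9 ≈ 331), equal allocation to each factor level. Assumed, because the article gives no visit-specific values: equal SDs of 1, complete balanced data among those analysed, and decay patterns whose mean pairwise correlation is 0.6.

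**The plan's own figures.** The article reports no standard error for these contrasts, so there is none to reproduce. Its power figure (above 0.80 at d = 0.15) was not reproduced: between-group formulas under a common correlation of 0.6 give 0.30 to 0.69 at N = 368. It would be 0.78 or more if 0.15 were a coefficient on −1/+1 coding, that is d = 0.30. That is a separate question, and nothing below depends on it.

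**Step 1, reported variance.** With complete balanced data the difference-in-differences estimate is the same under either covariance. The random-intercept fit estimates the average variance and the average covariance, so the modelled variance of any change is 2(1 − 0.6) = 0.8. Between factor levels, SE = √(0.8 × 4/331) = 0.098 SD at every visit.

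**Step 2, true variance.** If baseline and 12 months correlate at r, the variance of the change is 2(1 − r). The ratio of true to reported SE is k = √((1 − r)/0.4), and type I error is 2(1 − Φ(1.96/k)).

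- r = 0.5: k = √1.25 = 1.12, type I error 8.0%
- r = 0.4: k = √1.50 = 1.22, type I error 11.0%
- r = 0.3: k = √1.75 = 1.32, type I error 13.8%

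**Step 3, full patterns with mean correlation 0.6.**

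| Pattern | Baseline–12-month correlation | True 12-month SE | Reported/true SE | Type I, 12 months | Type I, 6 months | Type I, 6 weeks |
|---|---|---|---|---|---|---|
| Constant | 0.60 | 0.098 | 1.00 | 5.0% | 5.0% | 5.0% |
| Mild linear decay | 0.51 | 0.109 | 0.90 | 7.6% | 5.1% | 3.4% |
| Decay from 0.8 to a floor of 0.45 | 0.49 | 0.111 | 0.89 | 8.2% | 5.9% | 2.0% |
| Decay from 0.8 to a floor of 0.30 | 0.45 | 0.115 | 0.85 | 9.4% | 5.7% | 1.7% |
| AR(1) by visit number | 0.34 | 0.127 | 0.78 | 12.8% | 9.7% | 1.1% |
| Exponential by month | 0.30 | 0.130 | 0.76 | 13.8% | 6.5% | 0.1% |

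Coverage of the 12-month 95% interval falls from 92% to 86% down the decaying rows.

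**Step 4, Kenward-Roger.** For balanced complete data under compound symmetry, the Kenward-Roger test equals the split-plot t-test, here with (336 − 8) × 4 = 1,312 degrees of freedom, so the adjustment is almost nil. In 5,000 simulated null trials (8 × 42), 12-month rejection was 5.2% under constant correlation, 7.4% under mild linear decay, 13.4% under AR(1) and 13.9% under exponential decay.

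**Step 5, what is not affected.** The variance of the mean over all five visits depends only on the average variance and average covariance, which the random intercept reproduces. The SE ratio for that contrast is 1.00 in every pattern. Unequal variance alone also does little: with correlation fixed at 0.6 and SD rising to 1.3 or falling to 0.8, the 12-month ratio is 0.98 to 0.99, and type I error stays between 3.1% and 6.8% at every visit.

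**The case against.** The strongest reply is that the article presents its equations as mean structures and does not say that the residuals are independent with equal variance. A random intercept can be combined with a residual correlation, and an analysis plan not shown here may do so. That stands as a limit: the text does not rule out a richer structure. But it does name the random intercept as what accounts for the repeated measures, and the single correlation in the sample-size section fits that reading. The point therefore criticises a stated choice rather than a missing detail.

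The second reply is that the direction and size are assumed. That also stands. Nothing in the article documents decay; under constant correlation there is no error, and the milder patterns give only 7.6% to 9.4% at 12 months.

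Third, a reader might infer that wrong p-values would lead to the wrong components being kept. The article does not support this. The retention rule is an effect size, the first decision is at 6 months, and with complete data the estimate does not depend on the covariance. With dropout (10% planned by 12 months) the weighting of incomplete data does depend on it, but the size of that effect was not calculated.

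Fourth, a reader might infer that all Aim 1 tests are invalid. They are not: a component main effect averaged over all visits is unaffected.

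**Conclusion.** The point holds, conditionally. As written, with ordinary residuals, the Aim 1 model imposes one correlation on gaps from 6 weeks to 12 months, and Kenward-Roger does not mend that. If correlation decays around an average of 0.6, the 12-month change-from-baseline intervals are too narrow and the p-values too small, with type I error of about 8% to 14% for a baseline-to-12-month correlation of 0.5 to 0.3. The 6-month contrasts are mildly affected (about 5% to 10%, the upper end only under AR(1) by visit), and the 6-week contrasts are conservative.

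The article does not support saying that the 12-month standard errors are certainly too small, or that the retention decision is wrong. It does support changing the model: the alternative is valid whether or not correlation decays, and it costs almost nothing. This should be settled before analysis, but it does not threaten the design.

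**What to change.** For the continuous outcomes, replace the random intercept with an unstructured within-subject covariance over the five visits, and keep discrete time and Kenward-Roger. Pre-state one fallback for non-convergence: the random-intercept model with cluster-robust (sandwich) standard errors by participant. A Toeplitz fallback would fit poorly, because it gives all adjacent visits one correlation although their gaps run from 1.5 to 6 months. The sandwich fallback repairs the standard errors but leaves the weighting of incomplete data on the random-intercept covariance, so it should stay a fallback.

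The cost is a change of wording in the analysis plan and 5 × 6/2 = 15 covariance parameters instead of 2. The 13 extra are negligible with 368 participants. The article also allows generalized linear models; any outcome analysed that way needs its own covariance statement, because this specification does not carry over directly.

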## Introduction

### Background and rationale {6a}

Youth with persistent post-concussive symptoms (PPCS) pose a rising public health challenge. Estimates suggest up to 1.9 million youth less than 18 years old sustain a concussion annually in the USA [1]. While concussion normally resolves within days to weeks following injury, up to 30% of youth experience symptoms such as headache, mood alteration, sleep disruption, and difficulty concentrating lasting longer than 1 month, currently defined as persistent post-concussive symptoms (PPCS) [2–5]. PPCS confers marked functional impairment interfering with academic performance and social interaction, and resulting in decreased quality of life [6–8]. Individuals who develop PPCS represent a small proportion of those injured, yet a disproportionate number of those requiring subspecialty care [9, 10]. Research suggests premorbid mental health issues increase the risk of developing PPCS following concussive injury [11]. However, despite recognition of the relationship between mood and PPCS, the standard of care for PPCS does not currently include mental health intervention and instead revolves primarily around rehabilitative exercise [12]. It is thus imperative that we develop effective treatments for youth with PPCS that target mental health.

Over the past two decades, our interdisciplinary investigative team has conducted a series of epidemiologic, RCT, and implementation studies that constitute foundational research for the investigation outlined in this paper [13–17]. Through this work, we have documented the association between concussion injury and a broad profile of functional impairments among youth and adults. Our initial RCT established the feasibility and acceptability of the collaborative care (CC) intervention model for injured adolescents and their caregivers, and the recent larger R01 trial demonstrated the effectiveness of this approach [14, 15].

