### Objectives {7}

Our first aim is to determine which components of the CC approach (cf-CBT, PST, and CM) contribute significantly to improvements in distal outcomes, particularly concussive symptoms, and youth health-related quality of life (HRQoL), among a diverse sample of youth with PPCS. We hypothesize that over the course of the 12-month trial, families who receive cf-CBT, PST, or CM will demonstrate greater improvements in the primary outcomes compared to those who do not receive these components, but that these components will be differentially beneficial, suggesting that a streamlined intervention may be comparably effective. As part of this aim, we plan to examine the effect of intervention components on proximal outcomes including youth headache, mood and sleep, and parental distress regarding their child’s illness.

Our second aim is to assess the potential mediation of intervention component effects by postulated mechanistic factors including improvements in (a) youth self-efficacy, (b) parental protectiveness, and (c) parental self-efficacy regarding navigating their child’s concussion care. We hypothesize that youth receiving cf-CBT will report increased self-efficacy regarding CBT; that parents receiving PST will report decreased parental protectiveness; and that families receiving care management will report higher self-efficacy regarding managing their child’s concussion care.

Our third aim is to explore the moderation of intervention component effects by demographic factors including parental education level, youth race/ethnicity, and youth sex, and clinical factors, including youth depression and level of parent emotional distress.

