#### Assignment of interventions: allocation

##### Sequence generation {16a}

Randomization will occur in blocks according to a computer-generated random assignment and stratified by patient’s sex assigned at birth (male or female) and study site (Seattle, UTSW, or other community). Once the randomization spreadsheet is generated, it will be uploaded into the REDCap randomization module.

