Moderator analyses will assess whether each component impacts primary outcomes differentially based on demographic and clinical factors measured at baseline. For demographic factors, we will examine the variables of parental education (4-year college degree vs. less education); youth assigned sex at birth (male or female), and youth race/ethnicity (Hispanic, non-Hispanic white, and non-Hispanic non-white) as moderators. For clinical factors, we will examine youth depression at baseline (PHQ-9 score ≥ 10 vs. < 10) and parent distress (as measured by the PIP, dichotomized based on a median split). To test these exploratory moderators, the study team will first examine the two-way interaction of component groups by each factor measured at baseline. If a significant interaction is detected, the study team will conduct a subgroup analysis and examine each of the component effects using mixed model regression within the subgroup defined by the moderators.

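### Time since injury (1 to 12 months at entry) is neither a named covariate nor a moderator, and the displayed Aim 1 models could not use it to sharpen the component effects

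*Protocol article*

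**What the plan says.** All references are to the Protocol article.

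- **Entry.** Eligibility criteria {10} admits youth from 1 to 12 months after injury who have at least three new or worsening symptoms.
- **Randomization.** Sequence generation {16a} has allocation "stratified by patient’s sex assigned at birth (male or female) and study site". Time since injury is not a stratum.
- **Covariates.** Under Aim 1, X_i "is a vector of covariates including baseline injury severity, birth sex, and referring site". The list is worded as open, and time since injury is not on it.
- **Model form.** Both Aim 1 equations enter the covariates as a single term, γX_i, beside a random intercept. The extra interactions mentioned for the first equation are those among the three components and time. None crosses a covariate with time.
- **Target.** The intervention-by-time coefficients "estimate the mean differences between treatment arms in changes" at each later visit relative to baseline.
- **Moderators.** Aim 3 names "parental education (4-year college degree vs. less education); youth assigned sex at birth (male or female), and youth race/ethnicity", plus baseline depression and parent distress. Objectives {7} gives the same set, with "clinical factors, including youth depression and level of parent emotional distress" as the clinical factors.

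**The concern.** The background states that "concussion normally resolves within days to weeks following injury" and defines the trial's condition by symptoms that outlast one month. The entry window then spans eleven months. Surveys are timed from enrollment, so at the 6-month decision visit participants are between 1 + 6 = 7 and 12 + 6 = 18 months past injury. It is plausible, though not shown in the document, that a youth just past the first month improves faster on average than one close to a year out. If so, part of the spread in change scores can be predicted from a baseline value the trial must already hold.

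Two things are at stake. One is precision: a component is kept or dropped on an effect size of 0.20, so a free reduction in standard error is worth having. The other is a question left unasked: whether a component works differently soon after injury than late.

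**Working it through.** **No figure to reproduce.** The plan gives no association between time since injury and outcome. Its only power figure for component effects (above 0.80 at d = 0.15) is a separate matter. Read as an ordinary difference between factor levels, that figure was not reproduced, but nothing below depends on it.

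**Step 1: would a plain covariate help?** In the displayed models, subject i's change from baseline to visit j is Y_ij − Y_i0. Both terms contain γX_i + b_0i, so these cancel. With complete data, the component-by-time contrast and its standard error are essentially the same whatever X_i contains. Only a covariate-by-visit term can take variance out of change. So even if time since injury were an unlisted member of X_i, the printed model would barely use it.

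**Step 2: is there bias?** A simulation of 4,000 trials with 331 completers and no true component effect gave mean estimates within 0.005 of zero, with or without time since injury. When its correlation with change was 0.2, 0.3 or 0.4, adjustment lowered the standard error from 0.098 to 0.096, 0.097 to 0.094, and 0.098 to 0.090. The omission costs precision only.

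**Step 3: how much precision?** Inputs from Sample size {14}: N = 368, within-subject correlation ρ = 0.6, 10% attrition (368 × 0.9 = 331.2, or 165.6 per factor level), two-sided alpha 0.05. The effect size of 0.20 is the Aim 1 retention threshold. Assumed: R², the share of residual variance (of change, or of baseline-adjusted follow-up) that time since injury explains.

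- Standard error ratio = √(1 − R²)
- Equivalent extra participants = 368 × R²/(1 − R²)
- Residual SD = √(2(1 − 0.6)) = 0.894 for change, or √(1 − 0.6²) = 0.80 for ANCOVA on one follow-up

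| Assumed R² | SE ratio | Extra participants | Power at 0.20, change | Power at 0.20, ANCOVA |
|---|---|---|---|---|
| 0 | 1.000 | 0 | 0.530 | 0.624 |
| 2% | 0.990 | 7.5 | 0.538 | 0.632 |
| 5% | 0.975 | 19.4 | 0.551 | 0.646 |
| 10% | 0.949 | 40.9 | 0.573 | 0.669 |

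Over a wider range, R² of 1% to 15%, the standard error falls by 0.5% to 8%.

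**Step 4: does chance imbalance matter?** Assume uniform entry over 1 to 12 months: SD = 11/√12 = 3.18 months. For a component comparison of 184 with 184, the SE of the difference in mean time since injury is 3.18 × √(2/184) = 0.33 months, or 0.10 SD. At R² = 5% (r = 0.22) that is 0.10 × 0.22 ≈ 0.02 SD of outcome. For the eight cells of 46, the expected gap between the highest and lowest mean is 2.847 × 3.18/√46 = 1.33 months. That is 0.42 SD of time since injury, or about 0.09 SD of outcome. The ordinary SE of a difference between two such cells is √(2/46) = 0.21 SD.

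**The case against.** The strongest reply is that nothing here is an error. The covariate list is open-ended, the article condenses a fuller plan that is not shown, and time since injury may already be in that plan. This stands in part: the list alone does not prove the omission. But the equations are printed, and their form could not exploit the variable. The moderators are named as a definite set.

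Second, the resolution within days to weeks describes concussion in general. The trial enrolls those who did not resolve, and no passage gives a recovery gradient across months 1 to 12 within that group. This stands, and it is why the size is assumed. A reader might go further and infer that youth near 12 months have a fixed course. The documents do not say so.

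Third, a reader might infer that the omission distorts the component effects, or that the eight-group comparison is left with uncorrected imbalance. Randomization rules out the bias, and chance imbalance is already reflected in the standard errors. The imbalance is small for the component comparisons (Step 4).

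Fourth, a reader might infer that the trial cannot say for whom the package works. Five moderators are planned, so the gap is one further candidate. Aim 3 is exploratory, and the choice of moderators is partly a matter of judgment.

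**Conclusion.** The point holds as a nearly free improvement, not as a threat to validity. Time since injury spans eleven months at entry, must be known for eligibility, and is named neither as a covariate nor as a moderator. The displayed Aim 1 models could not use it to sharpen change-from-baseline effects even if it were included.

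The gain is modest: under the assumed R² of 2% to 10%, power at the retention threshold rises by about one to four percentage points. If time since injury explains almost nothing within persistent symptoms, the gain is close to zero. Not stratifying on it is no defect in itself. The planned analyses would leave open whether component effects vary with time since injury.

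**What to change.** In the analysis plan, prespecify time from injury to baseline as a continuous covariate (for example on the log scale) and its interaction with visit, in both Aim 1 models. The interaction is the part that matters, since the main effect alone changes little (Step 1). Leave the randomization unchanged. Optionally, add component by time since injury, kept continuous, as a further exploratory Aim 3 moderator. If the full plan already contains these terms, it is enough to confirm that.

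With five assessments, a linear term costs one degree of freedom for the main effect and four for its interaction with visit, five per Aim 1 model. No new data or visits are needed. Recruitment is expected to run to about January 2027 and follow-up to March 2028, and no interim analysis is planned, so the terms can be fixed before outcomes are analyzed.

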#### Primary outcome measures

Health Behavior Inventory (HBI): A 20-item questionnaire that assesses concussive symptoms on a 4-point scale, ranging from “never” to “often,” and yields total scores in cognitive and somatic domains. We will use the youth-report version with established reliability and validity in youth with sports injury [37].

Pediatric Quality of Life Inventory (PedsQL): A 23-item questionnaire that assesses physical, emotional, social, and school functioning. The scale includes youth-report and parent-report versions [38–40].

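### The rule for building the optimized intervention uses d = 0.20 to keep a component in one sentence and to leave it out two sentences later

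*Protocol article*

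**What the plan says.** The final paragraph of Aim 1 in the protocol article has three consecutive sentences on selecting components.

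- The first considers "any components or interactions demonstrating an effect size of 0.20 on either the HBI or PedsQL to be worth retaining in the optimized intervention".
- The second ranks the visits: "We will make our initial decision at 6 months, but will also examine 12-month HBI and PedsQL outcomes".
- The third says that effectiveness and efficiency will be balanced by "not including components that demonstrate a small effect (Cohen’s *d* = 0.20) at 6 or 12 months on the HBI or PedsQL".

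Earlier in Aim 1 the plan adds: "We will also test for interactions between components". No other section gives a numeric cutoff for selecting components.

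**The concern.** The first and third sentences name the same outcomes and the same value and give opposite instructions. An analysis plan can add detail to a rule, but it cannot carry out both of these sentences.

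The stake is the trial's main product. The Introduction says the refined intervention will hold only components that improve youth outcomes efficiently, and the Discussion promises an optimized intervention ready for wide use. This paragraph is the only place where estimates become a decision to keep or drop. While both sentences stand, the choice for a component near 0.20 could be made after the results are known, with text to support either choice.

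**Working it through.** **Step 1: the two sentences side by side**

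| | First sentence | Third sentence |
|---|---|---|
| Outcomes | HBI or PedsQL | HBI or PedsQL |
| Value | effect size 0.20 | Cohen's d = 0.20 |
| Visit | none stated (6 months follows in the next sentence) | 6 or 12 months |
| Action | retain | do not include |

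**Step 2: possible meanings of the third sentence**

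Reading A: a negation or a *less than* was dropped, and effects below 0.20 are left out. Reading B: the sentence means what it says, and effects of about 0.20 are too small to justify the sessions. Take the first sentence to mean *at least* 0.20, and three illustrative effects:

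| Component effect | First sentence | Third, reading A | Third, reading B |
|---|---|---|---|
| 0.05 | drop | drop | drop |
| 0.20 | keep | keep | drop |
| 0.30 | keep | keep | keep |

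The conflict therefore lies at and around 0.20. That region is not remote. The Sample size section reports earlier effects of the whole package of 0.26 to 0.32 (HBI) and 0.19 to 0.29 (PedsQL), and single components may well fall near 0.20. The word *small* does not settle the reading, because the same section also applies it to d = 0.15.

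**Step 3: what the visit wording leaves open**

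Even under reading A, failing to reach 0.20 at 6 or 12 months can mean failing at both visits (so passing at either keeps the component) or failing at either (so both must be passed). The second sentence suggests a third rule, 6 months alone.

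Inputs from the Sample size section: 368 participants, 10% attrition at 12 months, within-subject correlation 0.6.

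- Analysed: 368 × 0.9 = 331.2. The 12-month attrition is applied at both visits.
- SE of a present-versus-absent difference, in SD units, before using baseline: √(4/331.2) = 0.110.
- With ANCOVA on baseline: 0.110 × √(1 − 0.6²) = 0.088.
- With change from baseline: 0.110 × √(2 × (1 − 0.6)) = 0.098.
- Correlation between the 6- and 12-month estimates: ANCOVA (0.6 − 0.36)/(1 − 0.36) = 0.375; change score 0.5.

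Assumed, because the document does not say: the rule compares point estimates with 0.20; the true effect is 0.20 on both outcomes at both visits; the HBI-PedsQL correlation is 0.3 to 0.8. Simulating correlated normal estimates (400,000 draws per setting) gives:

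| Rule (either outcome) | Probability of keeping the component |
|---|---|
| 6 months only | 0.60-0.70 |
| either visit | 0.76-0.87 |
| both visits | 0.42-0.55 |

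The figures are consistent: P(both) = 2 × P(6 months) − P(either visit). For the change score at outcome correlation 0.3 this is 2 × 0.702 − 0.851 = 0.553. The 6- and 12-month verdicts differ in about 30-37% of trials.

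**Step 4: interactions**

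The first sentence gives no sign for an interaction of 0.20. For an interaction that is truly zero, on one outcome at one visit, an unsigned 0.20 is passed with probability 2 × [1 − Φ(0.20/SE)]. With SE 0.088 to 0.098 (effect coding, main-effect scale) this is about 0.02-0.04. With the SE doubled (a difference of differences averaged over the third component) it is about 0.26-0.31. By symmetry, half of these are antagonistic. The scale is itself unsettled: the plan says "we will use effect coding of variables for the three components" and then defines the indicators as 1 or 0.

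**The case against.** The strongest reply is that the intent can be recovered. The first sentence is worded as the criterion and the third as its rationale, and the stated aim of a streamlined package of effective components fits 0.20 as a minimum. A dropped word is the probable explanation, and the slip touches neither randomization nor estimation. Much of this stands: reading A is the likelier one. It remains inference, however. Reading B is coherent, nothing else in the article excludes it, and reading A still leaves the visit open.

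A reader might infer more than the document supports:

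- *That the same data justify keeping or dropping any component.* An effect near zero is retained by neither sentence, and one clearly above 0.20 is excluded by neither.
- *That an antagonistic interaction would be built into the package.* The hypotheses are directional, being worth retaining presupposes benefit, and the second set of Aim 1 analyses compares all 8 combinations to find the better ones, which would show antagonism.
- *That two visits compete on equal terms.* The second sentence puts 6 months first. Only the defective third sentence blurs this, and a tie-break is ordinary analysis-plan detail.
- *That the PedsQL adds a further chance to pass.* The outcome section does say "The scale includes youth-report and parent-report versions", and the assessment table lists both reporters, but choosing the reporter for a decision is commonly left to the analysis plan.
- *That the rule may retain nothing.* That would follow from the height of the threshold and whatever effects one assumes, and would be equally true of a consistently worded rule.

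**Conclusion.** Wrong as written. The component-selection threshold is given in opposite directions within one paragraph, and no other part of the article resolves it. This rests on the wording alone. It affects components whose effect is at or near 0.20.

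The blurred decision visit is secondary. Under the assumptions shown, the chance of keeping a component with a true effect of 0.20 runs from 42-55% to 76-87%, depending on how the last sentence is repaired. These figures illustrate the cost of leaving the visit open; they do not measure the keep-or-drop conflict. The missing sign for interactions would not be an error on its own, but it belongs in the same edit.

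**What to change.** Before any outcome results are seen, replace the third sentence so that the paragraph states one rule consistent with the first two. For example: *Components whose effect in the beneficial direction is below d = 0.20 on both the HBI and the PedsQL at 6 months will not be included, unless they take part in a synergistic interaction that reaches 0.20; 12-month estimates will be examined as supporting information on durability.*

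In the same edit, say that an interaction of 0.20 counts towards retaining a combination only if it is synergistic, and that antagonistic interactions are handled through the planned comparison of the 8 combinations. The scale of the interaction and the PedsQL reporter can be left to the analysis plan. If the sponsor did mean that effects of about 0.20 are too small to keep, the first sentence must change instead; either way one rule should remain.

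The cost is a few lines in a dated amendment, with no change to sample size, procedures or data collection. There is time: no interim analysis is planned, and the Trial status section expects full recruitment near January 2027 and the last follow-up by March 2028. The downside is that the sponsor commits in advance to one direction and one primary decision visit.
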